## Abstract

**Background:**

Shared Decision Making (SDM) is a way to empower patients when decisions are made about treatment. In order to be effective agents in this process, patients need access to information of good quality. Routine Outcome Monitoring (ROM) may provide such information and therefore may be a key element in SDM. This trial tests the effectiveness of SDM using ROM, primarily aiming to diminish decisional conflict of the patient while making decisions about treatment. The degree of decisional conflict, the primary outcome of this study, encompasses personal certainty about choosing an appropriate treatment, information about options, clarification of patient values, support from others and patients experience of an effective decision making process. Secondary outcomes of the study focus on the working alliance between patient and clinician, adherence to treatment, and clinical outcome and quality of life.

**Methods/Design:**

This article presents the study protocol of a multi-centre two-arm cluster randomised controlled trial (RCT). The research is conducted in Dutch specialised mental health care teams participating in the ROM Quality Improvement Collaborative (QIC), which aims to implement ROM in daily clinical practice. In the intervention teams, ROM is used as a source of information during the SDM process between the patient and clinician. Control teams receive no specific SDM or ROM instructions and apply decision making as usual. Randomisation is conducted at the level of the participating teams within the mental health organisations. A total of 12 teams from 4 organisations and 364 patients participate in the study. Prior to data collection, the intervention teams are trained to use ROM during the SDM process. Data collection will be at baseline, and at 3 and 6 months after inclusion of the patient. Control teams will implement the SDM and ROM model after completion of the study.

**Discussion:**

This study will provide useful information about the effectiveness of ROM within a SDM framework. Furthermore, with practical guidelines this study may contribute to the implementation of SDM using ROM in mental health care. Reporting of the results is expected from December 2016 onwards.

**Trial registration:**

Dutch trial register: TC5262

Trial registration date: 24th of June 2015

## Background

Shared Decision Making (SDM) is defined as an approach where clinicians and patients share the best available information when making clinical decisions, and where patients are supported to consider options to achieve informed preferences [1]. An important principle of Shared Decision Making is that there are at least two experts: the patient and the clinician. The process of SDM bridges both expert domains [2, 3]. SDM is seen as an intermediate stage between two extremes a traditional paternalistic and an informed choice model. In SDM the clinician and patient deliberate about treatment options and preferences. They select together the best suitable option which is consistent with patients’ values and preferences [2, 4, 5]. Elwyn et al. [1] describe three steps of SDM: 1) making sure that patients know that reasonable options are available 2) providing detailed information about these options, and 3) supporting the consideration of preferences and decision making about what will be the best choice.

A few studies testing SDM have been conducted in mental health care [2, 6], including a small number of randomised controlled trials and other types of studies, mostly focusing on psychosis and depression. They indicate that SDM contributes to better informed patients regarding the disease and treatment options. Furthermore, it stimulates patients to take an active part in decisions on treatment options. Also, SDM can have a positive influence on patient satisfaction, better acceptance of the agreed treatment, adherence to treatment and reduction of uncertainty by the patient about the decision taken [2, 7–13]. Finally, SDM increases the likelihood that treatment is delivered in accordance with guidelines. Few studies that tested this have found limited effects of SDM on reduction of symptoms [7, 9], mainly by the mediating variable treatment adherence on clinical outcome [9]. Despite the limited but promising results of SDM widespread implementation seems to be lagging behind [2, 14–16], while generally patients prefer greater participation than they are offered [13, 17, 18]. Patients with severe mental illness and depression have positive attitudes towards SDM, desire to be involved in decisions, and are also able to participate in decision making [10, 19–21].

ROM implies regular measurement of clinical outcomes aiming to improve quality of care. ROM provides clinical feedback as to the effectiveness of care for patients and clinicians which may be used to choose appropriate treatment options [22–27].

In a review Carlier et al. [28] found that feedback with ROM has positive effects on the behaviour of professionals with respect to faster and more appropriately screening to establish the correct diagnosis, more frequent and effective communication between patient and clinician, and, when appropriate, swifter adjustment of treatment. ROM appears to have a positive short term effect on mental health status [29] and, if ROM feedback was used in consultations, is especially beneficial for the monitoring of patients who are not responding to treatment, the so called Not-On-Track (NOT) patients [22, 23, 29–32]. The greatest reduction of symptoms takes place in the condition where both parties, patients and clinicians, were provided with feedback [22, 23]. Measuring outcome of patients on a regular basis during treatment will allow clinicians to identify non-responding and negatively responding patients before they leave their treatment. The sooner a clinician can be notified that a patient’s positive outcome is threatened, the sooner preventive actions can be attempted [33].

### Rationale

Both SDM and ROM are able to empower the patient during the treatment process and to provide good quality information in order to be a more effective agent in the decision making process. Such an approach was evaluated in an open pilot in a centre for patients with combined physical and mental disorders. The SDM approach during intake and treatment was combined with frequent ROM. In line with treatment goals, clinician and patient choose symptoms to be monitored with ROM during treatment. The progress in treatment is evaluated with six weekly monitoring used in a feedback cycle. This approach proves feasible, adherence of both patients and professionals is high and patients improve at symptom level. However, so far, a RCT evaluating such a combined SDM-ROM approach has not yet been performed [34]. The expectation is that systematically sharing the feedback about treatment progress derived from ROM within a SDM framework may help to empower patients, improve their involvement in clinical decision making and thereby enhance the quality of care. The SDM-ROM model should be applicable to different subgroups in mental health care.

### Aim and hypotheses

Our aim is to test whether the appliance of a model in which ROM and SDM are integrated is effective compared to decision making as usual where SDM using ROM is not implemented.

The first hypothesis is that the combined SDM-ROM model will lead to less decisional conflict experienced by patients which encompasses more personal certainty about choosing an appropriate treatment, good information about options, clarification of values, support from others and experience of an effective decision making process. Second hypothesis is that the application of the SDM-ROM model will improve the working relationship between patient and clinician, will increase patient’s adherence to treatment and will have positive effects on clinical outcome and quality of life.

## Methods/Design

### Trial design

The study is designed as a multi-centre two-arm cluster randomised controlled trial of Shared Decision Making (SDM) in specialised mental health care using Routine Outcome Monitoring (ROM) as a source of information. A cluster randomised design in which the unit of randomisation is the treatment team is deemed necessary to prevent spill-over effects between intervention and control groups. During recruitment of teams for the study, pairs of teams from the same mental health organisation are randomly assigned to either the experimental or control conditions (matched pairs). Control teams will implement the SDM and ROM model after the completion of the study.

### Participants and setting

The study takes place in specialised mental health care organisations. Due to the expected generic applicability of the SDM-ROM model, the model is being tested to various subgroups with the following characteristics: age (adolescents, adults and elderly patients), diagnosis (psychotic, common mental and personality disorders) and setting (outpatient, day-clinic and clinic). In this study, a total of six intervention and six control teams from four organisations participate. In accordance to the sample size calculation (ref. section sample size) the teams will include 364 patients (182 in the intervention group and 182 in the control condition, with an average of 31 patients per team). Patients who don’t speak and read Dutch are excluded from the study.

### Randomisation and blinding

The matched teams treat a similar population of patients, in a similar geographic catchment area in the Netherlands and have similar personnel. Randomisation of the teams is conducted through an independent data manager. Due to the randomisation at the team level and the nature of the intervention, blinding of the clinicians and patients is not possible. To avoid bias due to lack of blinding outcome parameters will be collected, independent of the research team, with self-report instruments to be completed both by patients and clinicians.

### Intervention

The intervention teams implement the SDM-ROM model with five steps (Table 1) both in the intake and treatment process.

**Table 1 Tab1:** SDM-ROM model

1. Introduction	➣ Refer to expectations about shared process.
	➣ Discuss which role the patient desires in decision making.
	➣ Connect with patient’s wishes and goals. ‘What does he/she want to achieve in treatment?’
	➣ Explain about ROM as an information source.
2. Give meaning to ROM	➣ Discuss ROM outcomes
	➣ Steps:
	Identify, Understand, Appreciate, Act.
3. Explore options	➣ Discuss options, advantages and disadvantages, in a neutral manner.
4. Weigh options	➣ Weigh advantages and disadvantages: ‘What’s for you important?’
5. Shared Decision	➣ Can a choice be made?
	➣ Select together most appropriate option.
	➣ Make follow-up appointments.

Shared Decision Making using Routine Outcome Monitoring as an information source (Step 1 to 5)

In order to ensure that the use of ROM by clinician and patient has added value in treatment, the intervention teams measure with appropriate questionnaires or rating scales at suitable moments minimal at the beginning, during and at the end of treatment. The type of ROM-instruments and frequency of measuring is not centrally prescribed, but in each intervention team tailored to the patient group. The appliance of the five steps SDM-ROM model is the key intervention. To implement the SDM-ROM model, the intervention teams follow a Quality Improvement Collaborative (QIC) program of 1 year, which can be considered as a multifaceted implementation strategy [35–37], consisting of a mix of improvement strategies, in which training and coaching in the SDM-ROM model are important components:

National:Three conference days for the intervention teams for exchange and learning, with the expert team and advisors from the national collaborative support organisation (Trimbos-institute, Netherlands Institute of Mental Health and Addiction, https://www.trimbos.nl/) present.Training and booster sessions for the clinicians participating in the intervention teams about the SDM-ROM model.A workshop about how to use ROM-instruments.A network of multidisciplinary teams.Experts providing supervision and advice about ROM best practices.Meetings between local team coordinators for exchange and learning, with the Trimbos-institute advisors present.Meetings for local patient representatives for exchange and learning.A QIC ROM website for exchange of presentations, publications, best practices and tools.

Local:Team visits and telephone contacts with Trimbos-institute advisors for advice and coaching.SMART goal setting, actions and indicators written in action plans (PDCA) by the local teams. Written feedback on local action plans by Trimbos-institute advisors.Teams organise meetings at their own location to work on their improvement plans. The teams plan, implement, evaluate and adjust their actions to improve the application of ROM as a tool in SDM (PDCA-cycle).Feedback to the local teams with a general survey about ROM in daily clinical practice (Trimbos-institute, 2015).Involvement of patient representatives in improvement teams.Active management involvement with the intervention teams.

### Data collection

#### Procedures

To prevent selection bias, clinicians in both groups invite all patients, based on date of the first treatment session, to participate in the study during a period of 6 months. In long term treatment teams, patients are selected by chronological order of treatment evaluation date. This group is also followed for a period of 6 months.

The clinicians of the intervention and control teams inform their patients about the study and obtain informed consent.

In case a patient is transferred to another clinician within the intervention team during the course of the study, the SDM and ROM process is transferred to this clinician. If the patient is transferred to another team during the treatment, for example from the intervention to the control team or vice versa, the patient can no longer participate in the study.

Data collection is conducted by independent research assistants outside the participating organisations. Depending on the frequency of consultations between clinician and patient using the SDM-ROM model, patients are completing self-report questionnaires at three times (baseline = T0, 3 months after baseline = T1, and 6 months after baseline = T2) or twice (baseline = T0 and 6 months after baseline = T2). In both frequencies of measurement the questionnaires for the study are sent after the SDM-ROM conversation. In addition, clinicians answer questions at T2 regarding their patients. Patients and clinicians who participate in the study receive a link by email to complete the questionnaires. If necessary, 1 week later they get a reminder by email. After 2 weeks an assistant phones the patients who have not yet answered the questions. If patients do not use internet, they receive paper questionnaires by mail.

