#### Secondary outcome measures

The secondary outcome measures (Table 2, Fig. 1) are the patient-clinician relationship, patient’s adherence to treatment, clinical outcome and quality of life. The patient-clinician relationship will be assessed using the Dutch version of the Working Alliance Inventory Short Form (WAI-S) [41–43]. For this study the WAI-S is chosen, because the questionnaire measures the quality of the alliance on the basis of three aspects related to SDM: contact/bond, agreement on goals and agreement on tasks [43–45]. Besides, the WAI-S has patient and clinician versions, which are both used in this study. The questionnaire consists of twelve questions concerning the agreement about treatment targets and tasks, and the interpersonal connection between patients and clinicians. The WAI-S scores from 1 (rarely or never) to 4 (always). Stinckens et al. [43] report a three factor structure of the patient version of the instrument: a contact/bond, a task and a goal component. Tracey et al. [41] also found evidence for one overall score. Psychometric qualities of the WAI-S proved to be good [41,43, 46, 47]. The scale correlates with outcome moderately. The perspective of the patient and a high score on the task scale are the strongest predictors for positive outcome [43].

In addition to these outcomes, the influence of the patients’ commitment to the treatment plan will be investigated. Data about no-show and drop out will be extracted from the electronic patient record by each team.

Finally, effects of SDM using ROM on treatment results will be studied with either the Manchester Short Quality of Live Measurement (MANSA-VN-16) [48] for long term patients or the Outcome Questionnaire (OQ-45) [49] for short term patients.

The MANSA-VN-16 is a self-report questionnaire which measures how satisfied the patient is in each of the following life domains: living situation, social relationships, physical health, mental health, safety, financial situation, work situation and life as a whole. Twelve questions are answered on a 7-point scale (1 = not satisfied, 7 = very satisfied) and four items are rated by ‘yes’ or ‘no’. An overall score of subjective quality of life can be calculated as a mean overall score. A higher score on the MANSA means a better quality of life. The psychometric properties are satisfactory [50].

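### Patients are recruited and consented after team randomisation by clinicians who know the arm, so date-order invitation protects only partly against selection bias; who extracts no-show and drop-out data also needs reconciling

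*Protocol article*

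**What the plan says.** On allocation, Trial design makes the treatment team the unit of randomisation: "A cluster randomised design in which the unit of randomisation is the treatment team is deemed necessary to prevent spill-over effects". It places allocation at the stage when teams join: "During recruitment of teams for the study, pairs of teams from the same mental health organisation are randomly assigned". The abstract adds: "Prior to data collection, the intervention teams are trained to use ROM during the SDM process". Randomisation and blinding accepts that "blinding of the clinicians and patients is not possible".

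On patient entry, Procedures (under Data collection) says: "To prevent selection bias, clinicians in both groups invite all patients", by date of the first treatment session, or in chronological order of evaluation date in long-term teams. It then says: "The clinicians of the intervention and control teams inform their patients about the study and obtain informed consent".

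On data collection, the same section states: "Data collection is conducted by independent research assistants outside the participating organisations". Secondary outcome measures states: "Data about no-show and drop out will be extracted from the electronic patient record by each team".

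**The concern.** In a cluster trial, randomisation makes the teams comparable. It makes the participating patients comparable only if entry does not depend on the arm. Here the person who explains the study and asks for consent knows the allocation and, in the intervention arm, delivers the model under test. If the study is presented differently in the two arms, different kinds of patients may agree. If willingness is related to decisional conflict, the Decisional Conflict Scale (DCS) comparison then carries a difference that is not a treatment effect.

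The limitations in the Discussion mention unblinded clinicians only in connection with extra effort by control teams and knowledge crossing over. Recruitment is not named.

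A second, narrower matter is that the general sentence on outside data collection does not fit the sentence that gives extraction of no-show and drop-out to each team.

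**Working it through.** **1. Order of events**

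| Step | Where stated | Consequence |
|---|---|---|
| Team pairs allocated as teams are recruited | Trial design | Arm is fixed before patients are invited |
| Intervention teams trained before data collection | Abstract, Methods/Design | Recruiting clinicians in that arm are already trained |
| Clinicians not blinded | Randomisation and blinding | Recruiters know the arm |
| Clinicians invite, inform and obtain consent | Procedures | Patient entry passes through them |

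**2. What each stated safeguard covers**

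- *Date-order invitation of all patients* (Procedures) fixes whom to approach. It does not fix how the study is explained or who accepts, and the clinicians apply the rule themselves.
- *Matched pairs* (Discussion) support comparability of teams, not of the patients who consent within them.
- *Covariate adjustment* (Statistical analyses) enters unevenly distributed variables; the examples are sex, age, education, diagnosis, length of treatment and locus of control. Willingness to take part is not measured.
- *T0 scores.* Procedures says the study questionnaires go out after the SDM-ROM conversation and makes no exception for T0. T0 scores in the intervention arm may already reflect the intervention, so a difference at T0 could not be assigned to recruitment.

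**3. The plan's own figures (Sample size)**

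Inputs: d = 0.5, α = 0.05 (sidedness not stated; two-sided assumed), 65 per arm, ICC 0.05, 25% drop-out, six teams per arm.

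- Analysed patients per team: m = 136/6 = 22.67
- Design effect: 1 + (22.67 − 1) × 0.05 = 2.083
- 65 × 2.083 = 135.4, rounded up to 136 per arm
- 136/0.75 = 181.3, rounded up to 182 per arm

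The stated 136 and 182 reproduce. This point disputes no sample size figure.

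**4. What a recruitment imbalance would do (assumed values only)**

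Standard error of the standardised difference: √(2/136 × 2.083) = 0.175.

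With no true effect and a spurious difference b, the two-sided type I error is 1 − Φ(1.96 − b/0.175) + Φ(−1.96 − b/0.175).

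| b (SD) | b/0.175 | Type I error |
|---|---|---|
| 0 | 0 | 5.0% |
| 0.05 | 0.29 | 5.9% |
| 0.10 | 0.57 | 8.8% |
| 0.20 | 1.14 | 20.8% |

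To show what such values of b would require: the mean of consenters differs from that of all eligible patients by (share not consenting) × (gap between non-consenters and consenters). With an assumed gap of 0.5 SD, equal in both arms, non-consent rates that differ by 10, 20 or 40 percentage points give 0.10 × 0.5 = 0.05, 0.20 × 0.5 = 0.10 or 0.40 × 0.5 = 0.20 SD. Equal rates give zero, and exchanging the arms reverses the sign. The article gives neither consent rates nor a gap.

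**5. Record outcomes**

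Procedures, in general terms: "Data collection is conducted by independent research assistants outside the participating organisations". Secondary outcome measures, for two items: "Data about no-show and drop out will be extracted from the electronic patient record by each team". Table 2 agrees with the second, listing both items with the electronic patient record as method and the organisation as source. Taken literally, the general sentence does not hold for these two items.

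**The case against.** The strongest defence is that the article does set a rule. In both arms all patients are invited, in date order, so as written the clinician has no choice of whom to approach. A reader might infer that protection against selection is absent. The text does not support that, because consecutive invitation is a real safeguard. What it leaves open is presentation and consent.

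A reader might also infer that team extraction exposes the trial's results in general to observer bias. It does not. The DCS is patient self-report, and assistants outside the organisations collect it. Team extraction concerns two record items. The independence claimed under Randomisation and blinding and in the Discussion is tied to self-report instruments, so record data do not contradict it; only the general sentence in Procedures conflicts. Nor does the article support saying that classifying drop-out calls for judgement. It gives no definition, but a full protocol or analysis plan commonly does, and that gap is no finding.

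It is also fair to object that covariate adjustment is planned and that any magnitude is invented. Adjustment helps with measured imbalance but cannot reach unmeasured willingness. The objection on magnitude stands in full: size and sign are unknown, and the range above illustrates sensitivity only.

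**Conclusion.** The point holds in limited form. Recruitment and consent follow allocation and are done by clinicians who know the arm. Date-order invitation is a partial safeguard, so describing it as preventing selection bias is an overstatement, and nothing in the stated analysis can reliably detect or repair what it leaves open.

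The size and direction of any bias are unknown. If it amounted to 0.05 to 0.20 SD, the two-sided type I error would be about 6% to 21% instead of 5%. That rests on 136 analysed patients per arm, an ICC of 0.05, a normal approximation and assumed values of the bias.

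The conflict over who collects the no-show and drop-out data is a separate and smaller matter. It concerns two adherence items and leaves the patient-reported primary outcome untouched.

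**What to change.** For recruitment:

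- Keep the existing date-order rule, but generate the list from the patient record instead of leaving it to the clinician.
- Use one arm-neutral information letter in both arms, posted by the team secretariat if privacy requires it.
- Have the existing outside research assistants explain the study and obtain consent.
- Log eligible, invited and consented numbers per team and compare them by arm.
- Describe the safeguard as partial, and name recruitment after allocation among the limitations.

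For the record outcomes, reconcile Procedures with Secondary outcome measures on who extracts no-show and drop-out. Extract both items under the same definition in both arms, by someone outside the treating team where record access allows. Extraction by the independent data manager is an option only: the article gives that role the randomisation and says nothing of record access.

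The cost is revised wording, some assistant time and a privacy arrangement for first contact. The assistants already send questionnaires and phone participants, but contact before consent would be new to them. Sample size and primary outcome stay as they are.

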The following three process scales will be used:Four questions for patients and clinicians, developed by the research team, about the added value and use of ROM feedback in the conversation between patients and clinicians. Patients in the intervention group will be asked to fill out the four ROM-questions at T0, T1 and T2. At T2 clinicians will complete the same questions regarding the consultations with their patients.The SDM-steps will be measured with the translated Shared Decision Making-Questionnaire-9 (SDM-Q-9), which has a version for patients and one for clinicians. Both versions ask the patient and clinician first to enter the health problem the consultation was about and which decision was made. The questionnaire continues with nine items about the steps in the SDM process, scoring at a six point scale that ranges from 0 (completely disagree) to 5 (completely agree). A total score can be calculated by summing the scores of all items. A high score indicates more SDM. The SDM-Q-9 shows a high reliability. The available results about the factorial validity are also positive [51, 52]. The SDM-Q-9 versions were translated into Dutch by the research team conform the standards of forward and backward translations (ref. section primary outcome measure, [40]). A recent publication about psychometric testing of a translated Dutch version of the SDM-Q-9 [53] demonstrated good acceptance, internal consistency, and acceptable to good convergent validity of the versions for patients and physicians. Patients in the intervention group will be asked to complete the SDM-Q-9 at T0, T1 and T2. At T2 clinicians will complete the same questions regarding the consultations with their patients.A general survey for clinicians of the intervention and control group at three moments in a year about ROM in daily clinical practice [50]. The survey consists of one question about the extent of using ROM in daily practice, with five response categories from ‘never’ to ‘always’. If a clinician scores ‘never’, the first question is followed by an open question about the reason(s) of this. After scoring the other answers, 23 statements about the implementation of using ROM will be submitted. The statements have five response categories, ranging from ‘strongly disagree’ (score 1) to ‘strongly agree’ (score 5). A higher score means a better implementation of ROM in daily practice. The development of the survey is described in a paper of the Trimbos-institute, Netherlands Institute of Mental Health and Addiction [54].

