
#### Patients’ characteristics at baseline: moderator and potential covariates

At baseline the following characteristics of patients (Table 4) will be collected: socio-demographics (sex, age, and educational level), diagnosis, length of treatment and locus of control. Locus of control is measured with the Mastery Scale [55]. This scale is designed to measure the degree to which people perceive that they can control factors that influence their life situation. The scale has been widely used and translated into multiple languages. Because no standardized scoring recommendations were provided, investigators developed their own scoring protocols and the studies are difficult to compare. The original Pearlin Mastery Scale showed good construct, predictive validity and internal consistency. The Dutch version, used in the baseline measurement of this study, consists of five negatively worded items with five ordered response categories from 1 (strongly agree) to 5 (strongly disagree), where 5 indicates the highest level of self-mastery. A total score can be calculated by summing the scores of all items (range 5–25). This version is also used in NEMESIS-I, a Dutch study of mental and physical health and wellbeing. The reliability of this version is good [55].

**Table 4 Tab4:** Patients’ characteristics

Topic & Instrument	Method	Patient	Clinician	Organisation
		T0	T0	T0
Patients’ characteristics at baseline				
Patient				
Educational level	SR	X		
Locus of Control-Mastery	SR	X		
Organisation				
Age	EPR			X
Sex	EPR			X
Diagnosis	EPR			X
Care domain	EPR			X
Length of treatment	EPR			X

*SR* self-report, *EPR* Electronical Patient Record

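### T0 is called baseline but is collected after the SDM-ROM conversation, so T0 self-report is post-exposure in the intervention arm and should not serve as a covariate or as a reference for change

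*Protocol article*

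**What the plan says.** Under Data collection, Procedures, the first measurement is labelled baseline: "patients are completing self-report questionnaires at three times (baseline = T0, 3 months after baseline = T1", with T2 at 6 months. Some patients skip T1, but every patient has T0. The same paragraph then fixes the mailing moment: "In both frequencies of measurement the questionnaires for the study are sent after the SDM-ROM conversation". No exception is made for T0.

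Other sections show what has happened by then in the intervention arm:

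- Abstract, Methods/Design: "Prior to data collection, the intervention teams are trained to use ROM during the SDM process".
- Intervention: "The intervention teams implement the SDM-ROM model with five steps (Table 1) both in the intake and treatment process", and "The appliance of the five steps SDM-ROM model is the key intervention".
- Treatment integrity: "Patients in the intervention group will be asked to complete the SDM-Q-9 at T0, T1 and T2". That questionnaire opens by asking what problem the consultation concerned and what was decided.

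For the control arm the abstract says "Control teams receive no specific SDM or ROM instructions and apply decision making as usual".

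Table 2 places the DCS, the patient WAI, the OQ-45 and the MANSA at T0. Table 4 places the Mastery scale (locus of control) there, and the text describes it with the words "The Dutch version, used in the baseline measurement of this study". Statistical analyses then says that variables found to differ between arms become covariates in the effectiveness tests. Locus of control is among its examples.

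**The concern.** A baseline is useful because the randomised treatment cannot have affected it. That property is what justifies adjusting for it or measuring change from it. Here the conversation that precedes the T0 mailing is the intervention itself, delivered by trained clinicians.

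The DCS asks how informed, supported and certain the patient feels about a choice, and the WAI asks about agreement with the clinician. Both could plausibly move after one such conversation. Mastery measures perceived control, and the Rationale expects the model to empower patients.

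Two things are at stake. The covariate rule as written can select Mastery for adjustment precisely because the intervention moved it, which takes part of the effect out of the estimate. And an analyst who trusts the label may use T0 DCS as the reference for change, as the start of an arm-by-time test, or as a covariate. Each of these is biased toward no effect if the first conversation already lowers decisional conflict.

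**Working it through.** **Is T0 before or after exposure?** Training precedes data collection, the model runs from intake, applying its steps is the key intervention, and the questionnaires follow the conversation. The SDM-Q-9 at T0 presupposes a consultation already held. No section describes a DCS, WAI, OQ-45, MANSA or Mastery measurement before that conversation. T0 is post-exposure in the intervention arm.

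**The plan's own sample size.** Inputs from Sample size and Participants: d = 0.5, α = 0.05 (two-sided assumed), power 0.80, ICC 0.05, six teams per arm, 25% dropout.

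- Individually randomised: 63 per arm by the normal formula, 64 by the t-test. The plan's 65 gives power 0.81.
- Design effect with m = 136/6 = 22.7 analysed per team: 1 + 21.7 × 0.05 = 2.08. Then 65 × 2.08 = 135.4, rounded up to 136.
- Dropout: 136/0.75 = 181.3, rounded up to 182; 182/6 = 30.3, hence 31 per team.

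The figures reproduce. They power a between-arm difference of 0.5, not a change.

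**What each contrast would estimate.** Take the DCS with SD 1, an effect of 0.5 at T2, a share f of that effect already present at T0, and within-arm T0–T2 correlation ρ. The documents give neither f nor ρ; both are assumptions shown over a range.

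- T2 level: estimate 0.5, SD 1.
- Change from T0, or the T0-to-T2 arm-by-time contrast: estimate 0.5(1 − f), SD √(2(1 − ρ)).
- T2 adjusted for T0 (ANCOVA): estimate 0.5(1 − ρf), residual SD √(1 − ρ²).

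Power uses the normal approximation with an effective n of 136/2.083 = 65.3 per arm, and the same design effect for every contrast.

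| Contrast | f | Estimate (ρ = 0.3 / 0.5 / 0.7) | Power (ρ = 0.3 / 0.5 / 0.7) |
|---|---|---|---|
| T2 level | any | 0.50 | 0.82 |
| Change or arm-by-time | 0 | 0.50 | 0.68 / 0.82 / 0.96 |
| | 0.25 | 0.375 | 0.44 / 0.57 / 0.79 |
| | 0.5 | 0.25 | 0.23 / 0.30 / 0.45 |
| | 1 | 0 | none beyond α |
| T0-adjusted | 0 | 0.50 | 0.85 / 0.91 / 0.98 |
| | 0.25 | 0.46 / 0.44 / 0.41 | 0.79 / 0.82 / 0.91 |
| | 0.5 | 0.43 / 0.38 / 0.33 | 0.72 / 0.70 / 0.74 |
| | 1 | 0.35 / 0.25 / 0.15 | 0.55 / 0.38 / 0.22 |

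A level difference averaged over T0 and T2 estimates 0.5(1 + f)/2. This is 0.375 at f = 0.5 and 0.5 at f = 1. It is a different target, but it counts the early effect instead of subtracting it.

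**The Mastery route.** If the intervention shifts T0 Mastery by a, and the within-arm slope of the outcome on Mastery is b, adjusting for Mastery changes the estimate from the total effect to the total effect minus a × b. Neither a nor b is in the documents, so this part has a direction but no size.

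**The case against.** The strongest reply is that the DCS harm depends on an analysis the protocol never adopts. Statistical analyses names linear regression and multi-level models. It names no change score, no arm-by-time test and no T0 DCS covariate, and those details may sit in an analysis plan that is not shown. This stands: a reader might infer that the primary analysis is biased as planned, and the document does not support that. It does not remove the point, because the mailing time, the baseline label and the covariate rule naming locus of control are all stated in the article. A later analysis plan cannot create a pre-exposure measurement.

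Second, rating the DCS after a decision suits the instrument, which needs a decision to rate. This also stands. The fault lies in calling that measurement baseline, not in taking it then.

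Third, f may be small. At f = 0.25 the T0-adjusted analysis has power 0.79 to 0.91 against 0.82 for T2 alone, because the smaller residual variance offsets the shrunken estimate. So it would be wrong to say that every T0-adjusted analysis risks missing a real benefit; its estimate is still too small.

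Fourth, it is tempting to say that T0 is tied to different events in the two arms. Procedures gives both arms the same inclusion anchor, the first treatment session or, in long-term teams, the evaluation date. What remains is that the control arm holds no SDM-ROM conversation and its mailing moment is not spelled out.

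Finally, two extensions are only inference: that long-term patients had several exposed contacts before T0, and that the OQ-45 and MANSA shift after one conversation. An immediate shift is less plausible for those two scales.

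**Conclusion.** The point holds in a limited form. T0 self-report is post-exposure in the intervention arm, and the covariate rule, followed as written, can adjust for a consequence of the intervention through Mastery. That requires Mastery to respond to the conversation, which is possible but not shown.

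The bias on the DCS is conditional twice over: on f being above zero, and on an analysis that uses T0 as a baseline. Under an assumed f of 0.5, a change or arm-by-time contrast would target 0.25 with power 0.23 to 0.45, and a T0-adjusted one 0.33 to 0.43 with power 0.70 to 0.74. A T2 level comparison keeps 0.50 and power 0.82. With f = 0 there is no bias.

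The documents do not show that T2 has to be the only primary time point. Nor do they show that a mailing window exists before the first conversation, since clinicians obtain consent and the model already runs at intake.

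**What to change.** 1. Describe T0 as the first post-conversation measurement, and treat T0 DCS and T0 WAI as outcomes.
2. State the primary test as a between-arm difference in level, either at T2 or averaged over the post-conversation measurements. Rule out change from T0, arm-by-time and T0-DCS adjustment as the primary test.
3. Restrict covariates to variables the intervention cannot affect: age, sex, diagnosis, length of treatment and educational level. Remove T0 Mastery unless it can be collected before the first conversation.
4. Send T0 in both arms after the same event, the first treatment or evaluation session that already defines inclusion.

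The cost is mostly wording. The statistical price is forgoing variance reduction from a DCS baseline: if f were really zero, T0 adjustment would have given power 0.85 to 0.98 instead of 0.82. The sample size is unchanged for a contrast at T2. If the averaged contrast is chosen, the plan should say that d = 0.5 refers to that average.
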